### Sample Size

The sample will be all patients with a first episode of ACS registered in CMBD-HA of ICS hospitals who meet all inclusion criteria and none of the exclusion criteria during the study period. In a previous study on patients with ACS conducted with SIDIAP database (publication pending) during the period 2009-2011, there were 3415 cases of ACS for all hospitals in Catalonia. Data from CMBD-HA of ICS hospitals corresponds approximately to 30% of all hospitals. Taking into account that our study period is 2006-2015 (10 years), we estimate to find approximately 3400 cases of ACS meeting inclusion criteria for our study.

### Variables

#### Exposure Definition

Patients will be classified as “exposed” to the study drugs (antiplatelet agents, beta-blockers, ACEI or ARB, statins) if they are prescribed any of them after the episode of ACS (up to two months after the event). The dose prescribed in ECAP will be considered the daily dose used for the patient, and the number of tablets contained in each package will cover the same number of days (see drugs of study in Table 2).

**Table 1 table1:** International Classification of Diseases, Nineth Revision (ICD-9) codes for endpoints of study and procedures.

ICD-9 code	Description
411*	Unstable angina and other forms of acute coronary heart disease
410*	Acute myocardial infarction
433*, 434*, 435*, 436*, 437*	Ischaemic stroke
00.66, 36.03, 36.09, 39.50	Coronary angioplasty

**Table 2 table2:** Anatomical, therapeutic, chemical classification system (ATC) codes for drugs of interest.

ATC code		Description of therapeutic group
**Study drugs**		
	B01AC	Platelet-aggregation inhibitors
	C07	Beta-blockers
	C09A, C09B	Angiotensin-converting enzyme inhibitors
	C09C, C09D	Angiotensin-receptor blockers
	C10AA, C10B	Statins
**Concomitant drugs**		
	C03	Diuretics
	C02	Antihypertensive drugs
	C08CA, C08D	Calcium-channel blockers (dihydropyridines/verapamil, diltiazem)
	B01AA, B01AB, B01AD, B01AE, B01AF, B01AX	Anticoagulants
	A10	Drugs used in diabetes mellitus
	C10AB, C10AC, C10AD, C10AX	Other lipid-lowering drugs
	C01A, C01B	Digoxin and antiarrhythmic drugs
	C01DA	Nitrates
	N05A	Antipsychotics
	M01A, N02BA, N02BB	Non-steroidal anti-inflammatory drugs

#### Adherence Definition

To estimate medication adherence, we will calculate the PDC for all four study treatments during eight months of follow-up after the index date. The PDC calculation is based on the packages dispensed and days of supply for each package, considering that the number of tablets contained in one package covers the treatment necessary for 28 or 30 days, depending on the drug. The information will be obtained from the pharmacy invoice data. For the PDC calculation, the numerator is the number of packages dispensed (invoice register) during the first 8 months of follow-up, and the denominator is the period of 8 months, which is the period for the adherence measure. Based on the PDC, patient adherence to each study drug is usually classified into one of two categories using the standard threshold of 75% (≥75%: adherent, <75%: nonadherent) [6,9]. PDC=75% accounts for six packages (each one including one month of drug treatment) dispensed during eight months. We define adherent patients as those who have received at least six packages during the first eight months after the event. Finally, according to adherence to all four study drugs, patients will be classified as adherent if they get the refill for all study drugs: PDC antiplatelet ≥75% + PDC beta-blockers ≥75% + PDC ACEI/ARB ≥75% + PDC statin ≥75%.

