The main objective of our study is to assess the relationship between adherences to the four pharmacological groups recommended for secondary prevention and the clinical outcomes of cardiovascular morbidity and mortality in patients with established CHD. The outcomes which are included as components of the composite endpoint are all-cause mortality, ACS, and ischaemic stroke. The secondary objectives are: 1) to assess the incidence of the composite endpoint in patients who are adherent to treatment with all four drugs compared with patients who are adherent to any combination of three, two or one drug, or no drug; 2) to assess the relationship between baseline sociodemographic and clinical characteristics and adherence to drug therapy; 3) to compare the number of days on sickness leave due to any cause according to adherence to drug therapy; 4) to estimate prevalence of use of the four drug treatments; and 5) to describe the posology prescribed for the four drug treatments.

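### The adherence numerator counts packages per drug group, not days covered, so the six-package rule can label a patient adherent well below the protocol's own 75% threshold

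*Protocol article*

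**What the plan says.** The Adherence Definition section of the protocol article first says that PDC rests on both the packages dispensed and the days of supply in each, "considering that the number of tablets contained in one package covers the treatment necessary for 28 or 30 days, depending on the drug". It then fixes the calculation: "the numerator is the number of packages dispensed (invoice register) during the first 8 months of follow-up". This count is set against a fixed window of eight months. The threshold is translated into packages: "PDC=75% accounts for six packages (each one including one month of drug treatment) dispensed during eight months". The operating rule follows: "We define adherent patients as those who have received at least six packages during the first eight months after the event".

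The section ends by requiring a PDC of 75% or more in each of four groups: antiplatelet, beta-blocker, ACEI/ARB and statin. Table 2 defines these groups by ATC class. The antiplatelet group, for example, is the whole of B01AC, "Platelet-aggregation inhibitors".

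The Exposure Definition section takes the dose recorded in ECAP as the daily dose, but adds that "the number of tablets contained in each package will cover the same number of days". The last secondary objective in the Introduction is "to describe the posology prescribed for the four drug treatments".

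**The concern.** A proportion of days covered should count each day once, however many agents of the group are in the patient's hands on that day. A package count does this only if every package holds the same number of days, no two packages overlap, and eight months is an exact multiple of the pack length. The protocol mentions days of supply, but they drop out of the numerator and of the six-package rule. No rule is stated for two agents of one group used together or for a switch within a group.

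This variable is the exposure for the main objective. It feeds the hazard ratios for adherence, the all-four-drugs classification and, in secondary objective 1, the number of drugs to which a patient is adherent. Overlap inflates the count, so the error it causes runs one way: patients who stopped early are placed among the adherent.

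**Working it through.** **Inputs.** From the Adherence Definition: numerator = packages; window = 8 months; cut-off = 6 packages; pack length = 28 or 30 days; threshold = 75%. Eight months is taken as 240 days (8 × 30) or, on the calendar, 8 × 365.25/12 = 243.5 days. From Table 2: groups are ATC classes, so a group can hold more than one agent.

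**The protocol's own figure.** 6/8 = 75%. In days, 6 × 30/240 = 75%. The stated equivalence reproduces for 30-day packs and a 240-day window.

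**One drug, once daily, 28-day packs.** 6 × 28 = 168 days, and 168/240 = 70.0% (168/243.5 = 69.0%). Seven packs are needed to reach 75%: 7 × 28/240 = 81.7%. With 30-day packs and 243.5 days, six packs give 180/243.5 = 73.9%.

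**Two agents of one group taken together, six packages in all, then nothing.** Days covered = the larger number of packs × pack length, because the other agent's packs fall on days already covered.

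| Split | Days covered (30-day packs) | Coverage of 240 days |
|---|---|---|
| 3+3 | 90 | 37.5% |
| 4+2 | 120 | 50.0% |
| 5+1 | 150 | 62.5% |

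For the 3+3 split, 28-day packs give 84/240 = 35.0%. With 243.5 days the two figures are 84/243.5 = 34.5% and 90/243.5 = 37.0%. The range is therefore 34.5% to 37.5%.

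**One switch within a group.** Use is sequential, so at most about one package overlaps. Minimum coverage is 5 × 30/240 = 62.5%, or 5 × 28/243.5 = 57.5% at the lowest. With no overlap and 30-day packs over 240 days it is 75%. The range is about 57.5% to 75%.

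**Two tablets a day.** The result depends on what a pack holds.
- If a pack holds one tablet per day of its nominal length, as the Exposure Definition implies, six packs cover 6 × 14 = 84 or 6 × 15 = 90 days: 84/240 = 35.0% or 90/240 = 37.5%.
- If each pack holds a month of treatment whatever the regimen, as the Adherence Definition assumes, six packs still cover six pack lengths and nothing is inflated.

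The document gives no pack contents, so the two sections have to be reconciled before this case can be sized.

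**The case against.** Four things can fairly be said for the plan.

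- **Pooling is inferred.** No sentence says that packages of different agents are summed; the text also speaks of adherence to each study drug and mentions days of supply. A condensed article may leave overlap rules to a fuller document. Part of this stands: pooling is read from the four-group formula and Table 2. But the article states the numerator and the cut-off outright, and those are not days covered. The 28-day discrepancy needs no pooling at all.
- **37.5% is a worst case.** It needs an equal split and then both agents stopped. A patient who drops one agent and keeps refilling the other up to 75% of days is adherent under either method. This stands.
- **The final class needs all four groups.** One inflated group changes the overall label only if the other three also pass. This stands, and it limits the effect on the four-drug classification.
- **Adjustment is planned.** Coronary angioplasty, type of index event and comorbidities are to be captured, and the Cox models adjusted. That addresses confounding in part, but it does not repair a mislabelled exposure.

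A reader might also infer that a within-group switch brings coverage down to about 37%. It does not: that would take three fully overlapping switches.

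**Conclusion.** The stated rule does not measure what the protocol says it measures. At the six-package cut-off, and if packages within a group are pooled as the text reads, two concurrent agents correspond to 37.5% to 62.5% coverage of 240 days with 30-day packs, depending on the split. The worst case is 34.5% to 37.5% over the pack sizes and window lengths considered. A single switch gives about 57.5% to 75%. Six 28-day packs of one drug taken once daily give 69% to 70%, so six packages and 75% are not the same rule on the protocol's own figures. The figure of 35% to 37.5% for two tablets a day is conditional on packs holding one tablet per day.

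Two stronger readings are not supported. One is that the misclassification is tied to prognosis: use of two agents may plausibly track procedure and severity, but the document does not show it. The other is that the hazard ratios are biased by a known amount or in a known direction: the document gives no frequency for any of these patterns, so the effect is unknown. What justifies the correction is that the rule is fixed for the main exposure and can be put right with data already planned.

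**What to change.** Define the numerator, for each group, as the number of distinct days in the window covered by at least one agent of that group.

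1. Convert each dispensing to a supply interval: pack content divided by the daily number of tablets recorded in ECAP.
2. Carry early refills of the same product forward.
3. Count a day once, whatever the number of agents, with a cap at 100%.
4. Divide by the number of days in the window, stated as a number.
5. Apply the 75% threshold to that proportion and delete the six-package rule.

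Reconcile the Exposure Definition and the Adherence Definition on what a pack covers, so that one tablet per day is not assumed in one section and a month of treatment in the other.

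The cost is programming work in a retrospective database study; pharmacy invoices and ECAP doses are already planned data. A default daily number of tablets has to be stated for patients whose ECAP dose is missing.

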### Study Population

The study population includes individuals ≥18 years with an incident diagnosis of ACS during the study period 2006-2015, with at least two months of follow-up in the Information System for Research in Primary Care (SIDIAP) [12] after the index date. The next patients will be excluded: pregnant women on the index date; patients with a recorded diagnosis of ischaemic stroke in the six months prior to index date; patients living in a nursing home on the index date; and patients with Alzheimer’s disease or other dementias.

Case definition: patient with an incident diagnosis of ACS registered in CMBD-HA (dataset of diagnoses at hospital discharge) [13] of the Catalan Health Institute (ICS) within the period from 2006-2015. Index date definition: date of ACS episode.

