### Data Collection and Data Sources

Diagnoses for study inclusion and endpoints will be obtained from CMBD-HA, which contains diagnoses at hospital discharge from all ICS hospitals, coded with International Classification of Diseases, Nineth Revision (ICD-9) [14]; see Table 1.

The rest of the variables will be captured from SIDIAP, which contains anonymized clinical information of all 279 PHC centres managed by the ICS in Catalonia (North-East Spain), covering a population of more than 5.8 million patients (about 80% of the total of 7.5 million population in Catalonia). The information contained in SIDIAP is registered by PHC general practitioners (GP), nurses and administrative staff in ECAP (electronic health records in ICS): comprehensive sociodemographic information, health conditions registered as ICD10 codes [15], specialist referrals, clinical parameters, toxic habits, PHC laboratory test results, GPs prescriptions and their corresponding pharmacy invoice data registered as Anatomical, therapeutic, chemical classification system (ATC) codes [16], date of sickness leave due to any cause, and date of death. Several reports have shown that SIDIAP data is useful for epidemiological research [17-25]. SIDIAP is listed under the European Network of Centres for Pharmacoepidemiology and Pharmacovigilance (ENCePP) resources database [26].

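### The fixed eight-month adherence window counts hospital days as days without drug, so the six-package rule asks more of patients who spend longer in hospital

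*Protocol article*

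**What the plan says.** Under Adherence Definition the protocol article fixes both parts of the proportion of days covered (PDC). For the top, "the numerator is the number of packages dispensed (invoice register) during the first 8 months of follow-up". For the bottom, "the denominator is the period of 8 months, which is the period for the adherence measure". The measure is taken "during eight months of follow-up after the index date", and Study Population gives "Index date definition: date of ACS episode". That section also draws cases from the hospital discharge dataset (CMBD-HA), so every patient has an index admission.

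The classification rule is the same for everyone: "We define adherent patients as those who have received at least six packages during the first eight months after the event". Its link to the 75% threshold is stated as "PDC=75% accounts for six packages (each one including one month of drug treatment) dispensed during eight months". All four drug groups must meet the threshold for a patient to count as adherent.

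The dispensing source listed under Data Collection and Data Sources is "GPs prescriptions and their corresponding pharmacy invoice data". No record of drugs given in hospital is listed. Nothing in the article deducts inpatient days, credits them as covered, or starts the window at discharge.

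**The concern.** A patient in hospital is normally given the drugs there and has no reason to collect a package from a pharmacy. Under the stated rule those days remain in the denominator and add nothing to the numerator. Two patients who refill equally well at home can then be classified differently because one spent longer in hospital. Since all four groups must pass, the same lost days lower all four PDCs together.

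The error is differential if patients with complicated index events or other serious illness have longer stays and a worse prognosis. They would be moved toward the nonadherent group because they are ill. That would make nonadherence look more harmful in the main hazard ratio, which is the result the article says it expects. It would also touch secondary objective 2, where comorbidity could seem to predict nonadherence merely through days lost to hospital.

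The Spanish cohort described in the Introduction, which is one of the two sources cited for the 75% threshold, measured PDC over nine months counted from hospital discharge. The protocol takes over the threshold but starts the clock earlier.

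**Working it through.** **Inputs.** Window: eight months, taken as 8 × 30 = 240 days from the ACS date (Adherence Definition, Study Population). Threshold: six packages. Days per package: 28 or 30 (Adherence Definition). Inpatient days in the window, d: not given in the document, so a range of 0 to 60 is assumed.

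**The plan's own figure.** 6/8 = (6 × 30)/240 = 75.0%, which reproduces. With 28-day packs the same six packages give 168/240 = 70.0%.

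**Reading A, packages counted as written.** The rule counts packages dispensed, not consumed, so the sixth may be collected on the last day. With the first fill at discharge, only five refill intervals have to fit into the 240 − d days at home. At refill rate c an interval lasts 30/c days, so 5 × 30/c ≤ 240 − d. The rate needed is therefore c = 150/(240 − d), and the total delay allowed over the five intervals is 240 − d − 150 = 90 − d days.

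**Reading B, days covered.** If six packages must cover 180 days at home, the coverage needed is 180/(240 − d), and the gap allowed is 240 − d − 180 = 60 − d days.

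| Inpatient days d | Reading A: 150/(240 − d) | Delay allowed (90 − d) | Reading B: 180/(240 − d) | Gap allowed (60 − d) |
|---|---|---|---|---|
| 0 | 62.5% | 90 | 75.0% | 60 |
| 10 | 65.2% | 80 | 78.3% | 50 |
| 20 | 68.2% | 70 | 81.8% | 40 |
| 35 | 73.2% | 55 | 87.8% | 25 |
| 60 | 83.3% | 30 | 100.0% | 0 |

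**Who changes class under Reading A.** A patient refilling at exactly 75% still reaches six packages while 240 − d ≥ 150/0.75 = 200, that is, up to 40 inpatient days. At 80% the limit is 240 − 187.5 = 52.5 days. With 28-day packs the rate needed is lower: 140/240 = 58.3% at d = 0 and 140/180 = 77.8% at d = 60.

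**Does planned adjustment remove it?** The covariates listed under Other Variables and its subsections include type of index event, angioplasty, comorbidities and the Charlson index. They do not include length of the index stay or later admissions. Readmissions occur after baseline, so baseline covariates capture them only indirectly.

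**The case against.** The strongest reply is that the rule as written is lenient. Packages dispensed are counted, so the starting requirement is 62.5% and not 75%, and only patients near the threshold or with very long stays change class. This stands. A reader might infer from the days-covered column that 60 inpatient days force perfect refilling. Under the package count, which is the rule the article states, they do not: the figure is 83.3%.

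Second, no stay lengths or readmission rates are given. Even on the stricter reading, 10 days move the requirement by about 3 points (75.0% to 78.3%). This also stands. A reader might conclude that the bias is large or would explain an observed hazard ratio, and the document gives no basis for that.

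Third, that hospital drugs leave no invoice is inferred from the description of sources and not stated. It is the natural reading, but it is an assumption.

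Fourth, the Cox models are adjusted for several severity markers. This reduces the problem but does not remove it, because time in hospital is not among them.

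Fifth, readmissions for ACS or ischaemic stroke are themselves endpoint events. They belong to the separate question of measuring exposure while outcomes accrue. The present point concerns the index stay and admissions for other causes.

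Finally, one could say that a condensed article leaves such refinements to a fuller document. That does not answer the point, because the article states the fixed denominator, the start date and the flat threshold outright.

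**Conclusion.** The point holds as a differential misclassification of modest or unknown size. The refill rate needed to be called adherent rises with days in hospital on either reading: from 62.5% to 83.3% over 0 to 60 inpatient days by package count, and from 75% to 100% by days covered. For short stays the shift is small.

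The direction, toward a lower apparent risk in adherent patients, rests on two assumptions: inpatient supply is not invoiced, and patients with more inpatient days have higher risk. Reading A also assumes 30-day packs first filled at discharge. The document supports neither a claim about how many patients are misclassified nor a claim about how far the hazard ratio moves. The rule merits correction before analysis because the remedy is cheap and uses a source already in the study.

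**What to change.** Start the adherence window at discharge from the index admission. Deduct later inpatient days recorded in CMBD-HA from the denominator. Define adherence to each drug group as days supplied covering at least 75% of the remaining days in the window. For a patient with r later inpatient days, the supply needed becomes 0.75 × (240 − r) days: 180 at r = 0, 165 at r = 20 and 135 at r = 60. Keep the fixed six-package rule as a sensitivity analysis, so that the effect of the change can be seen.

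The cost is a revised definition and some programming. The article describes CMBD-HA as a dataset of discharge diagnoses, so it must first be confirmed that admission and discharge dates can be extracted. The correction will be partial. Sample Size puts ICS hospitals at about 30% of all hospitals, and admissions or transfers elsewhere would not be seen. A reader might expect the index stay at least to be fully corrected, but a transfer out of an ICS hospital would break that, so this limit should be stated when results are reported.

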A large epidemiological study enrolled 7519 participants with established CVD from urban and rural communities in countries at various stages of economic development [10]. Use of antiplatelet drugs, beta-blockers, ACEI or ARB, and statins was assessed. Overall, 4421 (58.5%) individuals were not taking any of the four proven effective drugs, whereas 233 (3.1%) were taking all four drug types. Individuals recruited in high-income countries had had a CHD event or stroke a median of 6.0 years (interquartile range [IQR] 3.0–10.0) before inclusion. Although medication use increased in line with increase of country economic status, adherence rates in high-income countries were sparse too: 62.0% for antiplatelet drugs, 40.0% for beta-blockers, 49.8% for ACEI or ARB and 66.5% for statins.

A meta-analysis of randomised clinical trials assessed adherence to therapy comparing different dosing regimens in patients with chronic CVD.[11] The study showed that dosing regimens with once-daily administration, compared with two or more daily administrations, were associated with a significant 56% risk reduction of nonadherence to drug therapy (relative risk 0.44, 95% CI 0.35–0.54).

Due to the improvement of morbidity and mortality found with the quadruple drug therapy with antiplatelet, beta-blocker, ACEI or ARB, and statin in patients with established CVD, it is necessary to assess the long-term adherence to these drugs in the Catalan population and its relationship with cardiovascular events and mortality. Our hypothesis is patients with established CHD who adhere to drug therapy with the four recommended pharmacological groups have a lower risk of MACE and all-cause mortality compared with patients who do not adhere to drug therapy.

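### The fixed eight-month denominator counts a patient as nonadherent when the prescriber ends a whole drug group before the sixth package, so the comparison group mixes non-refill with prescriber withdrawal

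*Protocol article*

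**What the plan says.** The Adherence Definition section of the protocol article gives the whole rule. The bottom of the PDC ratio is the same for every patient and drug: "the denominator is the period of 8 months, which is the period for the adherence measure". The top counts dispensing only: "the numerator is the number of packages dispensed (invoice register) during the first 8 months of follow-up". The threshold is put into packages: "PDC=75% accounts for six packages (each one including one month of drug treatment) dispensed during eight months". The working rule follows: "We define adherent patients as those who have received at least six packages during the first eight months after the event". On pack size, "one package covers the treatment necessary for 28 or 30 days, depending on the drug". At patient level, "patients will be classified as adherent if they get the refill for all study drugs", with 75% required in each of the antiplatelet, beta-blocker, ACEI/ARB and statin groups.

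Other sections bear on the point:

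- **Exposure Definition** asks only for a prescription within two months of the event. It does not ask that the prescription continue.
- **Data Collection and Data Sources** says SIDIAP contains "GPs prescriptions and their corresponding pharmacy invoice data".
- **Table 2** lists anticoagulants and non-statin lipid-lowering drugs as concomitant drugs, outside the four study groups.
- **Patient Baseline Characteristics** are taken on the index date, and **Comorbidities and Clinical Parameters** as near to it as possible.

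No section ends the denominator when a drug is stopped, and none separates a stop by the prescriber from a patient who does not collect the drug.

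**The concern.** The hypothesis in the Introduction is about behaviour: adherent patients should have a "lower risk of MACE and all-cause mortality compared with patients who do not adhere to drug therapy". The classification measures something wider, namely whether a drug was dispensed for six of eight months for whatever reason. A patient who collected every package until the prescriber ended the group is placed with patients who did not collect what was prescribed.

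This matters for the hazard ratio because some withdrawals may follow a decline in health, and such a decline also predicts death, which is part of the primary composite. Those patients would raise the event rate in the nonadherent class for reasons unrelated to refilling. The decline occurs after the index date, so covariates fixed at or near that date do not record it. Secondary objective 2 is exposed as well: baseline characteristics that lead prescribers to stop a drug would appear as predictors of poor adherence.

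The problem would remain if the cohort were restricted to patients prescribed all four groups, because these patients were prescribed all four.

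**Working it through.** **Inputs.** From Adherence Definition: an eight-month window, a threshold of six packages, packs of 28 or 30 days, and all four groups required. From Exposure Definition: first prescription up to two months after the event. Assumptions made here: a 240-day window (8 × 30), first fill on day 0, 30 or 60, and a refill as each pack runs out.

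**The plan's own figure.** Packages divided by months: 6/8 = 75%. It reproduces.

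**Full refilling until withdrawal, 30-day packs, first fill on day 0.** PDC = packages dispensed before the stop ÷ 8.

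| Group ended on day | Packages | PDC, fixed denominator | Class |
|---|---|---|---|
| 30 | 1 | 12.5% | nonadherent |
| 60 | 2 | 25% | nonadherent |
| 90 | 3 | 37.5% | nonadherent |
| 120 | 4 | 50% | nonadherent |
| 150 | 5 | 62.5% | nonadherent |
| 180 | 6 | 75% | adherent |
| 210 | 7 | 87.5% | adherent |

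In every row, PDC over the time the drug was prescribed is 100%. Refill behaviour is identical throughout; only the date of the prescriber's decision changes the class.

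**Where the boundary lies.** Day of sixth fill = start day + 5 × pack length. The exposed share of the window after the start is 5 × pack length ÷ (240 − start day).

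| First fill | Sixth fill, 28-day packs | Sixth fill, 30-day packs | Exposed share |
|---|---|---|---|
| day 0 | day 140 | day 150 | 140/240 = 58% to 150/240 = 62.5% |
| day 30 | day 170 | day 180 | 140/210 = 67% to 150/210 = 71% |
| day 60 | day 200 | day 210 | 140/180 = 78% to 150/180 = 83% |

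**From group to patient.** Every group must reach 75%, so one group ended before its sixth fill is enough to make the patient nonadherent overall.

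**What counts as ending a group.** PDC is computed by group. A move from one statin to another, or from an ACEI to an ARB, keeps adding packages. A move from an antiplatelet to an anticoagulant, or from a statin to another type of lipid-lowering drug, does not, because Table 2 places the new drug outside the study groups.

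**The case against.** The strongest reply is that a fixed window is a deliberate and accepted convention. The Spanish cohort described in the Introduction also used the share of the follow-up period covered by dispensing, over nine months. Such a measure describes coverage, and whether a stop by the prescriber counts as lack of coverage is a matter of definition. This stands as a reason not to replace the primary definition. It does not answer the point that the hypothesis and conclusions speak of patients who do not adhere.

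A second reply concerns data. The article says prescriptions are held. It does not say that end dates, reasons, or who initiated the stop are recorded. A prescription may be closed because the patient had already given up the drug. A denominator that simply ended at the stop would also give 100% to someone treated for one month. These objections stand, and they favour a separate class in a sensitivity analysis over a new primary denominator.

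A third reply is that Concomitant Drug Use covers other medicines prescribed during follow-up, so a change to an anticoagulant would be visible. That stands in part. The wording there also speaks of baseline information, and use of another drug is only a proxy for withdrawal of a study group.

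A reader might infer that any withdrawal within the eight months produces misclassification. The package rule does not support that: a stop after the sixth fill, such as day 155 for a day-0 start, leaves the patient adherent. A reader might also put a percentage on the patients affected. With an assumed 3% to 8% chance of early withdrawal per group and independence between groups, the result is 1 − 0.97⁴ = 11% to 1 − 0.92⁴ = 28%. No rate is given in the document. Independence also conflicts with the idea that worsening health would end several drugs together; under complete overlap the same inputs give 3% to 8%.

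**Conclusion.** The point holds in a limited form. Under the stated rule, a patient with perfect refilling is classed as nonadherent overall when the prescriber ends an entire study group before the sixth package. The nonadherent class therefore combines two different things, and the planned covariates do not record deterioration after the index date.

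The boundary days rest on the 240-day window and prompt refilling. The mechanism itself follows from the package rule alone.

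A reader might go further and conclude that the hazard ratio is shown to be biased in favour of adherence. The document does not support that. It gives neither the frequency of prescriber withdrawal nor its reasons, and some withdrawals, for tolerability for instance, need not predict death. A bias making adherence look more protective is plausible, but its direction is not established and its size cannot be computed.

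**What to change.** Keep the fixed eight-month PDC as the primary definition. Add a prespecified sensitivity analysis of the primary hazard ratio with three classes built from the GP prescription records in SIDIAP/ECAP:

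1. adherent, as now defined;
2. did not refill while the drug was still prescribed;
3. a whole drug group ended by the prescriber before six packages, with no failure to refill while prescribed.

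The contrast of interest is class 1 against class 2. Report the size of class 3 and its event rate. If this result differs from the primary one, limit the conclusion to drug coverage and do not attribute it to patients' adherence behaviour.

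The cost is the use of prescription dates from a source the study already draws on, one extra category, and one extra model. Treatment, cohort and sample size are unaffected. The drawbacks should be stated with the result: end dates may be imperfect, some closed prescriptions will belong to patients who had already stopped, and the nonadherent comparison group becomes smaller, so its estimate is less precise.
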